## Abstract

**Aim:**

This article presents the study protocol of a retrospective cohort study designed to compare the effectiveness of herpes zoster, and influenza vaccines in individuals with multiple sclerosis (MS), chronic inflammatory bowel diseases (IBD), or chronic inflammatory rheumatic diseases (CIRD) to individuals without these diseases, using claims data of one of the largest population based health insurances in Germany.

**Background:**

Individuals with autoimmune diseases such as MS, IBD, and CIRD are more susceptible to vaccine preventable infectious diseases such as influenza and herpes zoster, due to the autoimmune disease itself, the presence of comorbidities and immunosuppressive therapies. Vaccines are the primary means to prevent such diseases. The efficacy of these vaccines is usually estimated using large randomized controlled trials, from which patients with MS, IBD, and CIRD are often excluded. It is therefore unclear whether these vaccines are also effective for these patients.

**Design:**

A target trial emulation based on observational claims data of a statutory health insurance company is proposed.

**Methods:**

This study will aim to emulate multiple target trials to compare the effectiveness of herpes zoster and influenza vaccines in patients with and without MS, IBD and CIRD using data from a large German statutory health insurance provider (BARMER). The primary outcome for each vaccine effectiveness analysis is the disease itself. The analysis will be carried out using both time-dependent matching and a multivariable Cox proportional hazards model in conjunction with g-computation. Additionally, the moderating effect of immunosuppressive therapies on the vaccine effectiveness will be estimated using a stratified secondary analysis.

**Discussion:**

This study will estimate and compare the effectiveness of influenza and herpes zoster vaccines in individuals with and without MS, IBD, and CIRD. Because of the large amount of data, this study will also be able to investigate the role of the immunosuppressive medication on vaccine effectiveness, which may provide guidance for vaccine administration guidelines.

## 1 Introduction

Individuals with autoimmune diseases, such as multiple sclerosis (MS), chronic inflammatory bowel diseases (IBD), or chronic inflammatory rheumatoid diseases (CIRD) have a highly increased chance of being infected with various vaccine-preventable infectious diseases (1, 2). This increased susceptibility, coupled with a higher chance of worse outcomes, has been shown repeatedly for MS patients (3), IBD patients (4, 5), and CIRD patients (6) compared to the general population and is thought to be the result of the autoimmune disease itself, existing comorbidities and the use of immunosuppressive therapies (5). Influenza and herpes zoster are two such diseases, which may lead to serious complications or even death (7, 8). The primary way to prevent these diseases in the general population is through the use of vaccines. The efficacy and effectiveness of these vaccines is usually determined using large randomized controlled trials, from which individuals with autoimmune diseases are often excluded (9). It is therefore unclear whether the effectiveness of the respective vaccines in individuals with autoimmune diseases is comparable to the effectiveness in individuals without these diseases.

Only a few studies tried to directly estimate the effects of herpes zoster or influenza vaccines in MS, IBD, or CIRD patients. Some single-arm prospective studies have shown an adequate immune response to an influenza vaccination in MS patients, but inconclusive results for pneumococcal vaccination in similar patients (10, 11). A few observational studies, based on routinely collected claims data, have demonstrated that vaccination against herpes zoster may be safe and effective in IBD patients (12–14), but the evidence for CIRD and MS is much more limited (15, 16). A meta-analysis of randomized controlled trials aiming to estimate the safety and effectiveness of the herpes zoster vaccine in both immunocompetent and immunocompromized patients in general also found the vaccine to be effective and safe (17), although it is unclear whether these results hold for MS or CIRD patients specifically.

This lack of evidence may be one reason why patients with autoimmune diseases are hesitant to get vaccinated, despite numerous recommendations and guidelines mentioning the benefits of vaccination (18–21). In this article we present a study protocol of a large-scale observational, retrospective study based on claims data from a large German statutory health insurance company that aims to compare the effectiveness of influenza and herpes zoster vaccines between individuals with and without MS, IBD, or CIRD. We first use the target trial framework to describe hypothetical randomized studies that we wish to emulate using the available data (22). Afterwards we give detailed explanations on how we will try to achieve this emulation. This includes a detailed description of inclusion criteria, definitions of treatments, outcomes and relevant confounders as well as an overview of the statistical analysis plan.

## 2 Methods and analysis

### 2.1 Aims and objectives

The primary aim of this study is to estimate the effectiveness of two different kinds of vaccines in individuals with either MS, IBD or CIRD and individuals without these diseases and to compare the effectiveness between these populations. More specifically, we are interested in the effectiveness of two types of vaccines:

Vaccines against herpes zoster (shingles).Vaccines against influenza.

A secondary aim of this study is to investigate the impact of immunosuppressive medication taken before vaccination on vaccine effectiveness in each of the three disease groups. It has been shown that the use of immunosuppressive medication raises the risk of developing infectious diseases (23). Since a large proportion of MS, IBD and CIRD patients receive such medications, disentangling the effect of the actual disease and the medication is crucial to make valid vaccine recommendations (24).

### 2.2 Target trials and target estimand

To make the aims of our study as clear as possible we formulate multiple *target trials*, as proposed by Hernán and Robins (22). A target trial is a description of a hypothetical study that we, the investigators, would conduct if there were no ethical or practical limitations on what we could do. It should include a description of all relevant study characteristics, such as inclusion- and exclusion criteria, a clear definition of the population of interest and how the study would be conducted. The aim is then to *emulate* these trials using available data and appropriate analysis techniques (22). This framework makes it easier to follow the International Council for Harmonization of Technical Requirements for Pharmaceuticals for Human Use guidelines (ICH-E9) for defining target estimands (25, 26) and allows us to formulate a clear definition of the time of inclusion of each patient (“time zero”) (27). Similar studies concerned with COVID-19 vaccine effectiveness have also used this approach effectively (28). Table 1 summarizes the most important components of the respective target trial protocols.

**Table 1 T1:** A summary of the most important protocol components for each of the planned target trial emulations.

**Protocol component**	**Target trial**	**Emulation with observational data**
Data Source	Prospectively collected data between 2013 and 2021.	Routinely collected claims data from a large German statutory health insurance company (BARMER) from 2013 to 2021.
Eligibility Criteria	(1) ≥ 18 years old (2) Biological sex of either male or female (3) No organ transplantation in the past 2 years (4) No cancer in the past 2 years (5) No autoimmune-related disease other than MS, IBD, or CIRD in the past 2 years (6a) For the herpes zoster trial: No previous herpes zoster vaccination (6b) For the influenza trials: No previous influenza vaccination in the current influenza season	Same as in the target trial, but with one additional criteria: (7) Enrollment in the BARMER health insurance company for ≥ 2 years with interruptions of no more than 5% of the total time
Treatment Strategies	(a) Vaccination against herpes zoster infection at treatment assignment with another vaccination between two and six months afterwards (b) Vaccination against influenza infection at treatment assignment (c) No vaccination at treatment assignment (no placebo) Treatment strategies (a) and (b) are compared to (c) in their separate trials.	
Treatment Assignment	Individual randomization, stratified on disease status (MS, IBD, CIRD or none of these).	To emulate randomization we adjust for multiple confounders using a combination of matching and g-computation.
Start and end of trial	(1) Herpes zoster vaccine effectiveness trial: 01.12.2018–31.12.2021^a^ (2) Influenza vaccine effectiveness trials:*^b^* (a) 01.09.2015–31.05.2016 (b) 01.09.2016–31.05.2017 (c) 01.09.2017–31.05.2018 (d) 01.09.2018–31.05.2019	
Start and end of follow-up	Start of follow-up: time of assignment to treatment strategy. End of follow-up: The earliest of death, loss-to-follow-up or administrative end-of-follow-up (end of the respective study).	
Outcomes	(1) Herpes zoster vaccine effectiveness: medically attended Herpes zoster infection (2) Influenza vaccine effectiveness: (a) medically attended influenza infection (b) severe medically attended influenza infection	
Causal contrast	(1) The ratio between the vaccine effectiveness (1 - the relative risk to develop the outcome at time *t* given the treatment) in the diseased group (individual has either MS, IBD or CIRD) and the non-diseased group (2) The vaccine effectiveness for each of the three disease groups (MS, IBD, CIRD), stratified by the categorized severity of received medication in regards to immunosuppressive effect. Both contrasts will be estimated as *intention-to-treat* and *per-protocol* effects. The target estimand is the average causal effect on the treated (ATT).	
Statistical analysis	Computing formal contrasts of simple Kaplan-Meier estimates.	Time-dependent 1:1 matching by days without replacement. Controls will be matched exactly by age in years, biological sex, place of residence, and disease status. The matched sample will be analyzed using a Cox model with additional adjustment for further confounders. G-computation based on this Cox model and a non-parametric estimate of the baseline hazard will be used to estimate the target estimand. Both *intention-to-treat* and *per-protocol* effects will be estimated by different censoring schemes as described in Section 2.6.3.
Sensitivity analysis	None.	The entire analysis will be repeated using *medically attended urinary tract infection* as a negative control outcome to assess the robustness of the confounder adjustment employed.
Reporting guideline	The results of the trial would be reported according to the *Consolidated Standards of Reporting Trials* (CONSORT) statement (78).	The results of the trial will be reported according to the *Reporting of Studies Conducted using Observational Routinely-Collected Health Data* (RECORD) statement (79).

a The 01.12.2018 is the first day from which the inactivated herpes zoster vaccine was recommended by STIKO (in german: “Ständige Impfkommission”) in Germany (29).

b Although information for two subsequent target trials (01.09.2019–31.05.2020 and 01.09.2020–31.05.2021) would be available, we choose not to try to emulate trials during this period because of the COVID-19 pandemic happening at the same time, which greatly impacted the spread and diagnosis of influenza.

Below we give a short first description of the considered target trials. More detailed information on the inclusion- and exclusion criteria as well as population definitions are given further below, because they are equal to the definitions used in the actual study. Due to the different nature of the considered vaccines, two different kinds of target trials will be described: one for the herpes zoster vaccination and one for each of the influenza vaccination trials.

The target trial for the herpes zoster vaccine effectiveness study starts at the first December of 2018, which is the date on which the vaccine became available in Germany. Each day from then on, people will be assessed for eligibility. If they meet the inclusion criteria, they are included in the study and are then randomized to either receive the vaccination (treatment group) or to receive nothing (control group). All individuals in the treatment group immediately receive the first dose of the vaccination. A second dose is administered after two to six months, in accordance to the current guidelines (29). All trial participants are followed up until the trial ends at the 31.12.2021. The primary outcome is then defined as the days until the occurrence of the main event of interest, where the start date is the date of trial inclusion for each individual.

The target trial for the influenza vaccine is very similar, but differs slightly due to the seasonality of the disease. Influenza viruses are constantly mutating, necessitating yearly changes of the influenza vaccines. It is therefore recommended to estimate influenza vaccine effectiveness on a seasonal basis instead (30). The target trial is therefore also defined on a seasonal basis, meaning that there is one target trial per influenza season that should be emulated. Recruitment would start each year on the first of September. People may then be recruited and followed up until the end of May of the next year (31.05.).

Both target trials are pragmatic, in the sense that no placebo control is used. We choose to formulate them this way because it is generally impossible to emulate placebo-controlled randomized controlled trials using only observational data (27). We further assume perfect adherence, so that every individual randomized to the treatment group actually receives the respective vaccination strategy and every individual in the control group does not. Our main interest is therefore in the *per-protocol* effect, although we will also estimate *intention-to-treat* effects in a sensitivity analysis, as described in detail in Section 2.6.3. Because we compare the vaccine effectiveness of patients with autoimmune diseases and other patients, but are unable to randomize the disease status itself, we are interested mainly in the *effect modification* of the disease status on the vaccine effectiveness (31). The result is a comparison of two population-based total causal treatment effects (32).

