#### 2.6.2 Analysis method

The matching process described above reduces the time-dependent vaccination variable to a time-fixed binary variable, allowing the use of well known analysis methods. We will first describe the matched data using descriptive statistics, stratified by treatment group and disease status. Means and standard deviations will be calculated for normally distributed continuous variables, median and ranges will be used for non-normally distributed continuous variables and counts and percentages will be calculated for categorical and binary variables. Appropriate statistical tests, such as *t*-tests and chi-squared tests, will be used to formally compare the distribution of these variables at baseline. Histograms and boxplots, stratified by both treatment groups and disease groups will also be drawn. In addition, the number of vaccinated individuals, matched controls and number of potential controls evolving over time will be graphically displayed as recommended by Thomas et al. (56).

For the estimation of the vaccine-effectiveness, we will employ standard time-to-event analysis methods, such as Kaplan-Meier curves and Cox models. No complex marginal structural models or similar strategies are required, because only information before inclusion into the trial is used for adjustment, making it impossible for *treatment-confounder* feedback (32) to occur.

Because we only match by age in years, gender, place of residence and disease status, we still have to adjust for the other confounders mentioned earlier to obtain unbiased estimates of the average causal effect we are interested in. A Cox model using the time to the respective outcome of interest as dependent variable and the treatment variable, the disease status and all relevant confounders (as observed at trial inclusion) as independent variables will be used to perform this adjustment. Since we are interested in the effect-modification of the vaccine effectiveness by disease status, we will also include an interaction term of these two variables in the model. This model, in conjunction with an estimate of the baseline hazard function (60), will then also be used to estimate confounder-adjusted survival curves using g-computation (61). These curves will then be used to derive time-dependent relative risk estimates, which will in turn be used to derive the vaccine effectiveness as (62):

(1)
$$\begin{array}{l} \theta \left(t\right)=1-RR\left(t\right), \end{array}$$

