by disease status, where *t* denotes the point in time and *RR*(*t*) is the relative risk of experiencing the respective outcome at time *t* in the vaccinated vs. unvaccinated group. Formal contrasts of the disease specific vaccine effectiveness estimates will then also be calculated. Cluster-robust standard errors will be used in the Cox model to adjust for potential dependencies introduced by matching (63). Non-parametric bootstrapping will be used to derive confidence intervals for the vaccine effectiveness and their formal comparisons. Although Abadie and Imbens (64) demonstrated analytically that bootstrapping is not a valid strategy to estimate standard errors in matched samples, it has been shown to work well in simulation studies (65). Due to these simulation results and a lack of alternatives we will therefore still rely on this method.

A very similar analysis strategy will be used to assess the moderating effect of the prior use of immunosuppressive medication on the vaccine effectiveness. In this analysis, only individuals with MS, IBD, or CIRD will be included. The entire analysis described above is then repeated, stratified by disease group and the severity of the received immunosuppresive medication (if any). Additionally, g-computation will be used to estimate the age-specific vaccine-effectiveness in each trial. To obtain a single estimate for the influenza vaccine, we will also use standard meta-analytic approaches to combine the estimates obtained from each of the four emulated influenza trials.

The proportional hazards assumption will be checked using Schoenfeld residual plots (66). If the assumption is deemed violated, we will try different strategies, such as inclusion of time-dependent hazard-ratios and variable transformations, to alleviate this issue. If these methods are unsuccessful, other models such as the additive hazards model (67) with a similar specification will be employed instead. In addition, we will perform a sensitivity analysis in which we will use a weighted Kaplan-Meier estimator instead of g-computation (68), where the weights will be estimated using entropy balancing (69).

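### The between-group contrast is a ratio of two vaccine effectiveness values, with no rule for a non-diseased value near or below zero, as expected in the negative control analysis

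*Protocol article*

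**What the plan says.** The primary aim (section 2.1) is to estimate VE in people with and without the three diseases and "to compare the effectiveness between these populations". Table 1, row on the causal contrast, gives contrast (1) as "The ratio between the vaccine effectiveness (1 - the relative risk to develop the outcome at time" t, taken "in the diseased group (individual has either MS, IBD or CIRD) and the non-diseased group". The article does not call this the primary contrast, but it is the one that answers the primary aim.

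Section 2.6.2 fits a Cox model with vaccine, disease status and confounders, and says of vaccine and disease status that "we will also include an interaction term of these two variables in the model". G-computation then yields risk curves, RR(t) and VE(t) = 1 − RR(t) by disease status. After that, "Formal contrasts of the disease specific vaccine effectiveness estimates will then also be calculated", and "Non-parametric bootstrapping will be used to derive confidence intervals for the vaccine effectiveness and their formal comparisons". The section names no scale for these contrasts and no rule for a VE at or below zero. For influenza, "we will also use standard meta-analytic approaches to combine the estimates obtained from each of the four emulated influenza trials"; the quantity pooled and its scale are not named.

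Table 1 (sensitivity analysis) and section 2.6.6 repeat the whole analysis with medically attended urinary tract infection, chosen because the vaccine does not directly cause or prevent it.

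**The concern.** A ratio of two VEs has a denominator that can pass through zero. Four things follow.

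- At non-diseased VE = 0 the contrast does not exist.
- Near zero, sampling error in the denominator gives very large values of either sign.
- When the two VEs differ in sign the ratio is negative and no longer reads as a share of protection retained.
- When both are negative the ratio is positive again and points the wrong way.

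At stake is the between-group comparison wherever VE is low. The plainest case is the check meant to support the main result. If confounding control works, urinary tract infection shows no vaccine effect in either group, and the contrast has no defined target. The robustness check would then be unreadable on this contrast exactly when it comes out well.

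**Working it through.** **Inputs.** From the article: the form of contrast (1), VE = 1 − RR(t), four influenza trials, bootstrap intervals, and a negative control that repeats the whole analysis. The article gives no expected VE, event count or sample size, so there is no figure of its own to reproduce. All VEs and event counts below are assumptions, shown over a range. Counts are control-arm events, diseased/non-diseased.

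**1. Algebra.** Ratio = (1 − RR_d)/(1 − RR_n).

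- Both negative, VE −0.1 (diseased) and −0.2 (non-diseased): (−0.1)/(−0.2) = +0.50. This reads as half the benefit, although the diseased group does better.
- A constant VE deficit of 0.10 in the diseased group:

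| Non-diseased VE | VE ratio | RR ratio |
|---|---|---|
| 0.60 | 0.83 | 1.25 |
| 0.40 | 0.75 | 1.17 |
| 0.20 | 0.50 | 1.13 |
| 0.10 | 0.00 | 1.11 |
| 0.05 | −1.00 | 1.11 |

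**2. Sampling behaviour.** Poisson events in 1:1 matched arms, VE = 1 − (vaccinated events/control events), 200,000 replicates. The ranges are the 2.5th to 97.5th percentiles.

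| Events | VE diseased / non-diseased | VE ratio | Ratio ≤ 0 | VE difference | RR ratio |
|---|---|---|---|---|---|
| 500/5,000 | 0 / 0 | about −40 to 40 | 51% | −0.14 to 0.12 | 0.88 to 1.14 |
| 500/5,000 | 0.05 / 0.05 | −2.04 to 5.84 | 22% | −0.13 to 0.12 | 0.88 to 1.14 |
| 500/5,000 | 0.10 / 0.10 | −0.23 to 2.40 | 5% | −0.13 to 0.11 | 0.88 to 1.14 |
| 500/5,000 | 0.20 / 0.20 | 0.44 to 1.56 | <0.1% | −0.12 to 0.10 | 0.87 to 1.15 |
| 500/5,000 | 0.30 / 0.40 | 0.49 to 0.99 | 0% | −0.21 to −0.01 | 1.01 to 1.35 |
| 1,000/20,000 | 0.20 / 0.20 | 0.61 to 1.37 | 0% | −0.08 to 0.07 | 0.91 to 1.10 |
| 100/1,000 | 0.20 / 0.20 | −0.37 to 2.40 | 7% | −0.28 to 0.22 | 0.73 to 1.36 |

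**3. Hand check of the 5% row.**

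- SE of log RR: non-diseased √(1/5,000 + 1/4,750) = 0.0203; diseased √(1/500 + 1/475) = 0.0641.
- RR ratio: combined SE √(0.0203² + 0.0641²) = 0.0672, so exp(±1.96 × 0.0672) = 0.88 to 1.14, as simulated.
- Denominator of the VE ratio: 0.05 with SE 0.95 × 0.0203 = 0.0192, only 2.6 SEs from zero. The numerator, with SE 0.95 × 0.0641 = 0.0609, is only 0.8 SEs from zero.

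**4. Negative control.** The row with VE 0 in both groups is the target there. More events do not help: with 1,000/20,000 the VE ratio runs from about −56 to 57, while the RR ratio narrows to 0.91 to 1.09.

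**5. Severe influenza, if events are few (assumed 20/200).** At VE 0.2 the VE ratio runs from −4.79 to 7.20, against 0.49 to 2.00 for the RR ratio. At VE 0.4 it runs from −0.56 to 2.19, against 0.45 to 2.10. The last case is mainly a shortage of diseased events, which costs precision on either scale.

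**6. Pooling, if the ratio were what is pooled (500/5,000 per season).** With equal VEs of 0.4, 0.3, 0.05 and 0.2 over the seasons, 22% of replicates had at least one non-positive seasonal ratio, so a log scale fails in those. Inverse-variance pooling on the raw scale gave 0.82 to 1.17.

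**The case against.** The VE ratio has a direct meaning, the share of protection retained, and it has the same null as the RR ratio. The RR ratio has a mirror-image weakness at high VE: it is 2.0 for 98% vs 99%, for 90% vs 95% and for 80% vs 90%. A narrower interval on the RR scale is not new information. The separate VEs are reported with intervals, so a reader can see when the denominator is small. All of this stands. It argues for keeping the VE ratio on show, but does not make it defined at a denominator of zero.

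A reader might also infer four stronger points that the article does not support.

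- *The ratio can never be interpreted or pooled.* The failure depends on VE and event counts; with adequate VE and events the ratio behaves well.
- *It must break down at early t, before protection develops.* Under the planned proportional-hazards model, RR(t) tends to the group's hazard ratio as t approaches 0, so modelled VE does not start near zero. Near-zero early VE could arise only with time-dependent hazard ratios, a replacement model, or the weighted Kaplan-Meier sensitivity analysis.
- *One weak season will wreck the pooled ratio.* The article says only that it will "combine the estimates obtained from each of the four emulated influenza trials". It does not say that the VE ratio is pooled or that a log scale is used, and raw-scale pooling held up above.
- *The fitted interaction being on the hazard scale is a defect.* G-computation exists to move from hazards to marginal risks.

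**Conclusion.** The concern holds in a conditional form. Contrast (1) is undefined at a non-diseased VE of zero and very unstable near it, and nothing in Table 1 or section 2.6.2 says what is then reported. For the negative control analysis this needs no assumed figures: no vaccine effect is the expected result under good adjustment. For weak influenza seasons and severe influenza it is a possibility whose size rests on assumed VEs and events. At 500/5,000 events and VE 5%, the VE ratio is not positive in 22% of samples. For herpes zoster there would be a problem only if VE were low, and nothing in the article indicates that. The analysis should be amended, but the study's main comparison is not invalid as a whole.

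**What to change.** In Table 1 and section 2.6.2:

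- Base inference on effect modification on RR_diseased(t)/RR_non-diseased(t) at a stated t, with its bootstrap interval and the VE difference beside it.
- Use the same contrast for the negative control analysis, where its expected value under successful adjustment is 1.
- Keep the VE ratio as a descriptive summary where non-diseased VE is clearly above zero.
- State what is pooled over the four influenza seasons. If a between-group contrast is pooled, pool log RRs or log RR ratios and back-transform.

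The cost is wording only, since the same g-computation curves and bootstrap samples give all three contrasts. The downside is that a ratio of relative risks reads less directly than the share of protection retained, which is why the VE difference or VE ratio should be shown with it.
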